## Abstract

Introduction: Stress at work and psychosocial risks are a major public health problem. Sophrology and neurolinguistic programming (NLP) have demonstrated benefits in terms of mental, physical and social health, both in the general population and in patients, and both in and out of hospital settings. However, these approaches have never been provided at the hospital for the benefit of health professionals at risk of suffering at work. In general, we aim to demonstrate the effectiveness of a hospital sophrology/NLP intervention for health care professionals at risk of stress-related disorders. The secondary objectives are to study (i) within-group, and (ii) between-group): (1) effects on mental, physical, and social health; (2) persistence of effect; (3) relationships between job perception and mental, physical, and social health; (4) intervention success factors (personality and job perception, attendance and practice, other); (5) effects on other stress biomarkers (other measures of autonomic nervous system activity, DHEAS, cortisol, etc.). Methods: Our study will be a randomized controlled prospective study (research involving the human person of type 2). The study will be proposed to any health-care workers (HCW) or any non-HCW (NHCW) from a healthcare institution (such as CHU of Clermont-Ferrand, other hospitals, clinics, retirement homes). Participants will benefit from NLP and sophrology interventions at the hospital. For both groups: (i) heart rate variability, skin conductance and saliva biomarkers will be assessed once a week during the intervention period (6 to 8 sophrology sessions) and once by month for the rest of the time; (ii) the short questionnaire will be collected once a week during the whole protocol (1–2 min); (iii) the long questionnaire will be assessed only 5 times: at baseline (M0), month 1 (M1), month 3 (M3), month 5 (M5) and end of the protocol (M7). Ethics and dissemination: The protocol, information and consent form had received the favorable opinion from the Ethics Committee. Notification of the approval of the Ethics Committee was sent to the study sponsor and the competent authority (ANSM). The study is registered in ClinicalTrials.gov under the identification number NCT05425511 after the French Ethics Committee’s approval. The results will be reported according to the CONSORT guidelines. Strengths and limitations of this study: The psychological questionnaires in this study are self-assessed. It is also possible that responses suffer from variation. For the study, participants need to attend 6 to 8 sophrology sessions and one visit per month for 7 months, which might seem demanding. Therefore, to make sure that participants will complete the protocol, two persons will be fully in charge of the participants’ follow-up.

## 1. Introduction

Work stress and psychosocial risks are a major public health problem [1,2,3]. Health care workers (HCW) are particularly at risk [4,5,6,7,8,9,10]. Moreover, non-HCW (NHCW) staff of hospitals can also be at risk [11,12], with working environment described as the main risk factor [9,13]. The University Hospital (CHU) of Clermont-Ferrand is one of the three CHU in France with more than 10% absenteeism, and the first CHU for duration of sick leave. The political orientations favor an approach to improve the quality of life at work. Sophrology is a mind–body method used as a therapeutic technique or experienced as a philosophy of life. It is an exclusively verbal and non-tactile method. It combines a set of techniques that will act both on the body and on the mind through breathing exercises, muscle relaxation and mental imagery (or visualization). It allows us to find a state of well-being and to activate all physical and psychological potential in order to acquire a better knowledge of oneself [14]. Neurolinguistic programming (NLP) is a set of communication and self-transformation techniques that focuses on reactions rather than the origins of behaviors [15]. NLP associated with sophrology proposes above all to mobilize the resources of the unconscious. Although the level of evidence varied between studies (observational studies or randomized controlled trials with limited quality) [16,17], some research tend to support the effectiveness of NLP strategies in the improvement of mental health (anxiety and depression), physical, and social health in the general population [18], in individuals with social/psychological problems [17], and in patients [19,20,21]. For sophrology intervention in patients, the number of studies available is scarce despite some benefits reported in literature [14,22]. Additionally, these approaches have never been provided in the hospital for the benefits of workers at risk of stress-related disorders.

In general, we aim to demonstrate the effectiveness of a hospital sophrology/NLP intervention for HCW at risk of stress-related disorders. Stress and well-being will be the target of the intervention and will be measured both in a subjective (questionnaire) and objective (biomarkers) way. The main objective is to demonstrate an improved heart rate variability in the intervention group during the period between month 1 (M1) and M3 (sophrology sessions) of the intervention group in comparison with the same control period M1 to M3 of the “deferred intervention” group. The secondary objectives are to study for the following comparisons ((i) within groups: comparisons between and M0 to M7 by randomization group and (ii) between groups: comparisons at M5 and then between M0 and M7): (1) the effects of the intervention on mental, physical, and social health; (2) the long-term effects of the intervention; (3) the relationships between the perception of work and mental, physical, and social health; (4) the factors of success of the intervention (personality and perception of work, attendance rate, quality of personal practice, etc.); and (5) the effects on other biomarkers of stress such as other measures of the activity of the autonomic nervous system, DHEAS, cortisol, etc.

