### 2.2. Study Settings

We will recruit any HCW or any NHCW from a healthcare institution (such as CHU of Clermont-Ferrand, other hospitals, clinics, retirement homes, EHPAD, etc.), who will be randomized in two groups: (i) the intervention group will have a longitudinal follow-up of seven months in total (a control period of 1 month, then 6 to 8 sophrology sessions during two months, then a 4-month follow-up); (ii) the control group will have a differed intervention (longitudinal follow-up of seven months in total beginning by a control period without intervention of 3 months, then 6 to 8 sophrology sessions during two months, then a 2-month follow-up).

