### 2.4. Eligibility Criteria

The inclusion criteria are to be an HCW or an NHCW from a healthcare institution (such as CHU of Clermont-Ferrand, other hospitals, clinics, retirement homes), between 18 and 65 years, with a stress greater than or equal to 50 on a visual analogue scale (VAS) of stress, to be able to give an informed consent to participate in research and to be affiliated with a Social Security scheme. The exclusion criteria are to have psychiatric, cardiovascular (heart failure, arrhythmia, etc.), hepatic (liver failure, etc.), renal (kidney failure, etc.), or endocrinological diseases (diabetes, etc.) judged by the investigator to be incompatible with the study because they may interfere with the measurements. Persons who are non-affiliated to a health insurance or protected persons (minors, pregnant women, breastfeeding women, guardianship, curatorship, deprived of freedoms, safeguard of justice) or persons who refuse to participate are not included.

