#### 3.3.2. Analyses for the Secondary Outcomes

Randomized groups comparison will be carried out (i) as aforementioned for continuous secondary endpoints and (ii) for categorical endpoints using Fisher exact tests or chi-squared. The results will be introduced using median difference and 95% confidence intervals estimated using quantile regression model for non-Gaussian data. The results will be presented using absolute differences and 95% confidence intervals for categorical parameters. The multivariable analysis related to dichotomous endpoints will be generalized linear mixed model, with logit link function, and center as random-effect. The results will be expressed with of relative risks and 95% confidence intervals.

Longitudinal data will be analyzed using random-effects regressions, modeling between and within participant effect, as random-effect, in addition to session effect. These analyses will concern (i) within groups comparisons between and M0 to M7 by randomization group and (ii) between groups: comparisons at M5 and then between M0 and M7). For between groups comparisons, the following fixed effects will be studied: randomization group, time-points evaluation and their interaction. 

Subgroup analyses will be conducted to explore potential influence of sex, occupation, stress at baseline, and previous sophrology experience on the primary outcome. Interaction terms in the regression models will be used to test for heterogeneity of effect between subgroups.

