## 4. Discussion

The World Health Organization defines health as “not merely the absence of disease or infirmity but a state of complete physical, mental and social well-being” [56]. In fact, the role of well-being at work plays a major role in social well-being [57]. HCW are particularly at risk [4,5,6,7,8]. Moreover, NHCW staff of hospitals can also be at risk [11,12], with working environment described as the main risk factor [13]. Indeed, the medical staff, especially those working in emergency departments are exposed to psychosocial risk factors because of the type of work they do [58,59]. Moreover, the COVID-19 pandemic has worsened the situation all around the world [60,61,62]. In general, HCW are confronted with the death of patients and the distress of their families [63]. 

Sophrology is a mind–body method used as a therapeutic technique or experienced as a philosophy of life. It helps to regain a state of well-being and to activate all physical and psychological potentials in order to acquire a better knowledge of oneself [14]. NLP is a set of communication and self-transformation techniques that focuses on reactions rather than on the origins of behaviors [15]. NLP combined with sophrology proposes above all to mobilize the resources of the unconscious.

This protocol seems particularly interesting for the University Hospital (CHU) of Clermont-Ferrand because it is one of the three CHU in France with more than 10% absenteeism, and the first CHU for duration of sick leave. By proposing sophrology to professionals at risk of suffering at work, this study design will allow us to observe a short-term effect (the first 3 months) and a long-term effect (4 months follow-up). This study will provide important data about the benefits of sophrology and NLP for workers at risk of stress-related disorders.

Articles related to this study protocol will follow the CONSORT recommendations for reporting randomized trials.

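### For secondary outcomes the named between-group comparisons are M5 and M0 to M7, but the control arm is treated from M3 to M5; the one treated-versus-untreated window, M1 to M3, is named only for the primary HRV outcome

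*Protocol article*

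**What the plan says.** Section 2.2 of the protocol article sets the two schedules. The intervention arm has "a control period of 1 month, then 6 to 8 sophrology sessions during two months, then a 4-month follow-up". The control arm has a "control period without intervention of 3 months, then 6 to 8 sophrology sessions during two months, then a 2-month follow-up".

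The Introduction names M1 to M3 as the between-group window for the main objective, HRV. For the secondary objectives, which include effects on mental, physical and social health, long-term effects and other stress biomarkers, it gives "between groups: comparisons at M5 and then between M0 and M7", together with within-group comparisons from M0 to M7.

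Section 3.3.2 repeats this for the longitudinal analyses: "ii) between groups: comparisons at M5 and then between M0 and M7". The fixed effects there are group, time point and their interaction. An earlier paragraph of the same section says that continuous secondary endpoints are compared by the methods already described for the primary endpoint, without restating a time window.

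The Discussion says that the design will show "a short-term effect (the first 3 months) and a long-term effect (4 months follow-up"). Sections 2.6 and 3.2 (Table 1) show that the long questionnaire is completed at M0, M1, M3, M5 and M7. The biomarkers are taken weekly during sessions and monthly otherwise. M1 and M3 data will therefore exist for the secondary outcomes.

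**The concern.** After M3 there is no untreated comparator. At M5 the intervention arm is two months past its sessions and the control arm has just finished its own; at M7 the arms are four and two months past. A difference at either visit shows how far the effect has faded relative to a more recently treated arm. It does not show whether the intervention works, or how much effect remains compared with never having had it.

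If these comparisons are read as tests of benefit, a fully lasting effect looks the same as no effect, and a fading effect looks like harm. The secondary objectives on effect and on long-term effect are tied to these comparisons. M5 is the only single visit named, so a reader who follows the list would test the secondary outcomes at a visit that cannot answer the question. Choosing M3 after seeing the data would be open to the charge of being post hoc.

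**Working it through.** **Schedules side by side (section 2.2)**

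| Period | Intervention arm | Control arm |
|---|---|---|
| M0–M1 | untreated | untreated |
| M1–M3 | sessions | untreated |
| M3–M5 | follow-up | sessions |
| M5–M7 | follow-up | follow-up |

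Only M1–M3 sets a treated arm against an untreated one.

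**The plan's own figure.** Section 3.1 gives effect size 0.5, two-sided 5%, 90% power and 85 per group. The normal formula n = 2(1.960 + 1.282)²/0.5² gives 84.1, rounded up to 85. The t-test version gives 85.03, and power at 85 is 0.90. With 15% loss, 85/0.85 = 100. Both stated figures reproduce and are not in dispute.

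**What each visit's difference estimates.** Let θ(t) be the effect against no intervention, t months after sessions end, taken as equal in both arms. Differences are intervention minus control, with positive values meaning benefit.
- M3: θ(0)
- M5: θ(2) − θ(0)
- M7: θ(4) − θ(2)

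**Illustration.** Three assumptions are not in the documents: that the 0.5 SD effect, stated in section 3.1 for HRV only, applies to the secondary outcomes; that a fraction r of the effect is kept per two months; and that the arms are equal. Then θ(0) = 0.5, θ(2) = 0.5r and θ(4) = 0.5r². The M5 difference is 0.5(r − 1) and the M7 difference is 0.5(r² − r). Rejection rates are for a two-sided 5% t-test with 85 per arm.

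| r | M5 difference (SD) | Rejection rate | M7 difference (SD) | Rejection rate |
|---|---|---|---|---|
| 1 | 0 | 0.05 | 0 | 0.05 |
| 0.75 | −0.125 | 0.13 | −0.094 | 0.09 |
| 0.5 | −0.25 | 0.37 | −0.125 | 0.13 |
| 0.25 | −0.375 | 0.68 | −0.094 | 0.09 |
| 0 | −0.5 | 0.90 | 0 | 0.05 |

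For r = 0.5 at M5 the noncentrality is 0.25 × √(85/2) = 1.63. Every non-zero difference favours the control arm. The M3 contrast, at 0.5 SD, has power 0.90.

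**The M0–M7 model.** Across M0, M1, M3, M5 and M7 the differences are 0, 0, 0.5, 0.5(r − 1) and 0.5(r² − r).
- A group main effect averaged over the five visits is 0.5/5 = 0.10 SD at r = 1, (0.5 − 0.25 − 0.125)/5 = 0.025 SD at r = 0.5, and 0 at r = 0. Its power is 0.05 to 0.17, taking a within-person correlation of 0.3 to 0.7 (assumed).
- Under the same assumptions the omnibus group-by-time test keeps power of about 0.81 to above 0.99, because M3 is among the visits. It tests all visits jointly, so a significant result does not say whether it comes from benefit at M3 or from the control arm catching up or overtaking later.

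**Recovering persistence.** Let the arms differ, with subscripts I and C.
- M3 + M5 differences = θ_I(2) + [θ_I(0) − θ_C(0)]. This is the 2-month effect if the end-of-session effects are equal.
- M3 + M5 + M7 differences = θ_I(4) + [θ_I(0) − θ_C(0)] + [θ_I(2) − θ_C(2)]. This is the 4-month effect only if the 2-month effects are equal as well.

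Numerical check at r = 0.5: 0.5 − 0.25 = 0.25 = θ(2), and 0.25 − 0.125 = 0.125 = θ(4).

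**The case against.** The case on the other side has real force on several points.

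- **M0 to M7 contains the clean window.** A reader might infer that every listed comparison falls after the control arm's sessions, so that none can show benefit. The documents do not support that. M0 to M3 precedes those sessions, and a model with group, time point and interaction gives a separate difference at each visit if time is categorical, M3 included. Only a group main effect would pool treated and untreated periods. This stands; what remains is that no M3 contrast is named and the omnibus test does not isolate it.
- **The primary window may carry over.** The reference back to the primary methods for continuous secondary endpoints could bring M1 to M3 with it. That reading is plausible, but the text does not say so, and the objectives in the Introduction name other time points. It is an ambiguity to resolve.
- **The numbers are scenarios.** The retention fractions appear nowhere in the documents, and the 0.5 is stated for HRV. A reader might take 0.37 as a forecast; it is one point in a range from 0.05 to 0.90. The sign of the M5 and M7 differences under fading depends on equal effects in the two arms, not on the size chosen.
- **Regression to the mean.** Entry requires participants "with a stress greater than or equal to 50 on a visual analogue scale", and a reader might infer that this explains a definite share of within-group improvement. The documents do not say when the eligibility score is taken, and section 2.5 separates the inclusion visit from the baseline measure, so some of the regression may occur before M0. No size can be derived from the documents, and the argument concerns the stress score, not every secondary outcome.
- **Little is lost beyond recovery.** The primary contrast is explicit and clean, section 3.3 calls most secondary analyses exploratory, and the M3 data will be collected. Figure 1 and the separate analysis plan are not at hand and might name M3. This lowers the weight of the point without removing it, because the list is stated twice and names M5 rather than M3.

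**Conclusion.** The point holds in a limited form. The M5 and M7 between-group differences compare two treated arms and cannot by themselves estimate benefit or long-term effect against no intervention. They do carry information on decay. The only treated-versus-untreated window is not explicitly named for the secondary outcomes, although the planned model can supply it.

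Under the illustrative assumptions, the M5 difference lies between 0 and −0.5 SD with rejection rates from 0.05 to 0.90, always against the intervention arm when non-zero. The M7 difference is at most 0.125 SD in size. The M3 contrast has power 0.90. That there is no untreated comparator after M3 follows from section 2.2 alone and needs none of these assumptions.

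The plan should be corrected before analysis, but the primary M1 to M3 comparison of HRV is unaffected and the trial's main conclusion is not at risk.

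**What to change.** Change the objectives in the Introduction and the text of section 3.3.2 as follows.

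- Name the M3 difference adjusted for M1, taken from the planned group-by-time model, as the between-group efficacy contrast for the effect-type secondary outcomes: objective 1 (mental, physical and social health) and objective 5 (other biomarkers).
- Label the M5 and M7 between-group differences as early-versus-deferred comparisons, informative on decay and not on benefit.
- If a persistence estimate is wanted, use the sum of the M3 and M5 differences for the 2-month effect, assuming equal end-of-session effects in both arms. Add the M7 difference for the 4-month effect, assuming equal 2-month effects as well. State both assumptions.
- Label within-group changes as descriptive. They have no concurrent control, and the stress threshold at entry may cause some regression to the mean in the stress score.

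The cost is wording and specified contrasts from a model already planned; no new data are needed. The downside is a wider interval for the persistence estimate and its reliance on the two assumptions.

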## 2. Materials and Methods

### 2.1. Study Design

Our study will be a randomized controlled prospective study (research involving the human person of type 2). The study design is described in Figure 1. The duration of participation per individual is 7 months for both the intervention and the control group. Randomization will be computer-generated.

### 2.2. Study Settings

We will recruit any HCW or any NHCW from a healthcare institution (such as CHU of Clermont-Ferrand, other hospitals, clinics, retirement homes, EHPAD, etc.), who will be randomized in two groups: (i) the intervention group will have a longitudinal follow-up of seven months in total (a control period of 1 month, then 6 to 8 sophrology sessions during two months, then a 4-month follow-up); (ii) the control group will have a differed intervention (longitudinal follow-up of seven months in total beginning by a control period without intervention of 3 months, then 6 to 8 sophrology sessions during two months, then a 2-month follow-up).

#### 2.2.1. The Intervention: Neurolinguistic Programming and Sophrology

Each participant will benefit from an NLP and sophrology intervention. The sophrology/NPL program will be provided by a qualified sophrologist outside from the hospital and that will be specifically employed by Clermont-Ferrand University Hospital for the purpose of this study, in order to avoid any previous relation between volunteers and the therapist. NLP and sophrology will take place within the University Hospital of Clermont-Ferrand. A total of 6 to 8 sessions will be proposed for each participant, by group of up to fifteen participants. Two sophrology sessions will be offered per week at two different times for easier accessibility. Each session will last one hour. They can take place in a seated or standing position, without physical contact. The sessions will consist of breathing exercises, visualization, and dynamic relaxation as well as concentration exercises. Breathing exercises have two objectives: (1) to manage the stress using deep inspiration and short expiration; (2) to dynamize the body using pauses between inspiration and expiration. During visualization process, we will ask participants to think of something or someone reminding pleasure and sensation of fullness. Dynamic relaxation includes exercises mobilizing parts of the body in order to take consciousness of all body segments. Breathing exercises, visualization, and dynamic relaxation are tools that should lead to an improvement of the dimensions of concentration (physical, mental, and emotional). All exercises will be guided by sophrologist. The sophrology/NLP program is standardized. Each session will take place in a typical way: (i) dialogue between the sophrologist and the participants, which makes it possible to specify the objective(s) of the session as the sophrologist will ask more specific questions to adapt the content of the sophrology session that they propose if they think it will be useful; (ii) presentation of the conduct of the session (possible variations) and instructions promoting autonomy; (iii) this practice is guided by the sophrologist, with the goal being to help free individuals from tensions, to play down a situation that worries and finally to realize that we can deal with. Sophrology exercises are adapted to the difficulties encountered by the participants; and (iv) time for free expression after the practice to promote the integration of the technique while giving elements to the sophrologist to guide the rest of the sessions.
